### Sample size

The under-five mortality rate in Jigawa was reported as 192/1000 livebirths in 2017 [26], and deaths in the first week of life may reasonably account for 15% of the total under-five deaths. More recently, a participatory radio programme on child health and COVID-19 was delivered across the LGA (June–December 2020) and vaccine coverage has increased (unpublished data), which we assume to have reduced mortality. We therefore used a conservative baseline mortality of 100 deaths amongst children aged 7 days to 59 months per 1000 livebirths. With the following parameters, we will have a minimum detectable effect size of 30% [6]: (a) 380 children per cluster, (b) 80% power, (c) 5% significance, (d) intra-cluster correlation of 0.007 [27] and (e) coefficient of variance of cluster size of 0.74. We assume on average there are three children under-five per compound (i.e. 127 compounds per cluster), and therefore, we will sample 4480 compounds overall to allow for ~ 10% loss to follow-up. The sample size was calculated using Stata’s *-clustersampsi-* command [28]. We will review these assumptions following the baseline survey.

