**Methods:**

This is a cluster randomised controlled trial, with integrated process and economic evaluations, conducted from January 2021 to September 2022. The trial will be conducted in Kiyawa Local Government Area, Jigawa State, Nigeria, with an estimated population of 230,000. Clusters are defined as primary government health facility catchment areas (*n* = 33). The 33 clusters will be randomly allocated (1:1) in a public ceremony, and 32 clusters included in the impact evaluation.

The trial will evaluate a locally adapted ‘whole systems strengthening’ package of three evidence-based methods: community men’s and women’s groups, Partnership Defined Quality Scorecard and healthcare worker training, mentorship and provision of basic essential equipment and commodities. The primary outcome is mortality of children aged 7 days to 59 months. Mortality will be recorded prospectively using a cohort design, and secondary outcomes measured through baseline and endline cross-sectional surveys.

Assuming the following, we will have a minimum detectable effect size of 30%: (a) baseline mortality of 100 per 1000 livebirths, (b) 4480 compounds with 3 eligible children per compound, (c) 80% power, (d) 5% significance, (e) intra-cluster correlation of 0.007 and (f) coefficient of variance of cluster size of 0.74. Analysis will be by intention-to-treat, comparing intervention and control clusters, adjusting for compound and trial clustering.

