### Outcome

The primary outcome is under-five mortality. This is defined as the number of children aged 7 days to 59 months reported to have died over a 12-month period who resided in sampled compounds (numerator), divided by the total number of children aged 7 days to 59 months who reside in sampled compounds (denominator). Deaths in the first week of life are excluded due to the challenges of accurate reporting of stillbirths and early neonatal deaths [20], and we do not expect the intervention to impact perinatal causes. Secondary outcomes are detailed in Table 3 and are based on the INSPIRING Programme Theory of Change.

**Table 3 Tab3:** Primary and secondary outcomes

Primary outcome	Definition
Under-five mortality rate	The number of confirmed* deaths amongst children aged 7 days–59 months, per 1000 livebirths reported by women in the cohort, in the last 12 months

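### The sample size treats an under-five mortality per 1000 livebirths as the 12-month death risk of each resident child, so expected deaths and the stated 80% power are overstated

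*Protocol article*

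**What the plan says.** The Sample size section starts from a published figure: "The under-five mortality rate in Jigawa was reported as 192/1000 livebirths in 2017". It suggests that first-week deaths may be 15% of the total, cites recent programmes that may have lowered mortality, and concludes: "We therefore used a conservative baseline mortality of 100 deaths amongst children aged 7 days to 59 months per 1000 livebirths". The abstract repeats this as "baseline mortality of 100 per 1000 livebirths".

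The other inputs are "a) 380 children per cluster, (b) 80% power, (c) 5% significance" and "d) intra-cluster correlation of 0.007 [27] and (e) coefficient of variance of cluster size of 0.74". The origin of the 380 is given: "We assume on average there are three children under-five per compound (i.e. 127 compounds per cluster"). The claim that follows is "we will have a minimum detectable effect size of 30" per cent.

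The Outcome section counts deaths over 12 months, "divided by the total number of children aged 7 days to 59 months who reside in sampled compounds (denominator"). Table 3 instead expresses the same outcome per 1000 livebirths in the last 12 months. The Analysis section fixes the period as July 2021 to June 2022 and uses a logistic model.

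**The concern.** A mortality per 1000 livebirths for ages 7 days to 59 months describes what happens to a birth cohort over nearly five years. The 380 are a cross-section of living children of all ages under five, each observed for at most 12 months. Multiplying one by the other credits each cluster-year with about five years of deaths.

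A rough check needs no demographic assumption. A 10% yearly risk sustained for five years gives 1 − 0.9^5 = 0.41, or about 410 deaths per 1000 by age five. That is more than twice the 192 per 1000 from which the article starts, and about four times the 100 per 1000 it meant to assume.

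Readers will judge a non-significant mortality result against the stated power and detectable effect. If the trial can reliably detect only a larger reduction, that result says much less about a 30% effect than the article implies.

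**Working it through.** **Inputs from the article.** 32 clusters analysed, taken as 16 per arm; m = 380 children per cluster; ICC 0.007; CV of cluster size 0.74; control risk 0.10; 30% reduction; 5% significance, taken as two-sided.

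**Input not in the article.** Resident under-fives per annual livebirth, s. A stationary population with 10% mortality gives about 4.7, and annual growth of 3–3.5% about 4.3. The range used is 4.2 to 5.

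**Formulas.** Design effect DE = 1 + ((1 + CV²)m − 1) × ICC. Effective n per arm = 16m/DE. Power is the normal approximation for two proportions with pooled variance under the null.

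**Step 1: the article's own figure.**
- DE = 1 + (1.5476 × 380 − 1) × 0.007 = 5.11.
- Effective n = 6080/5.11 = 1190 per arm, against 1356 needed.
- For 0.10 against 0.07, the null standard error is 0.01143 and the alternative 0.01142. (0.03 − 1.96 × 0.01143)/0.01142 = 0.665, so power is 75% and the detectable effect about 32%.

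This is near the stated 80% and 30%, though not equal to them. It gets this close only when 0.10 is the risk of each of the 380 children.

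**Step 2: match the units.**
- 12-month risk per resident child = 0.10/s = 0.020 (s = 5) to 0.024 (s = 4.2).
- Equivalently, 380 residents correspond to 380/s = 76 to 90 births a year, and 7.6 to 9.0 deaths per cluster-year rather than 38.
- Over 32 × 380 = 12,160 children at the control risk: 243 to 290 deaths, against 1,216 implied by 10%. The overstatement is 4.2- to 5-fold.

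**Step 3: clustering at the lower risk.** The between-cluster coefficient of variation is k = √(ICC(1 − p)/p). At p = 0.10 and ICC 0.007, k = √0.063 = 0.25. Holding k gives ICC = 0.063p/(1 − p) = 0.0013 to 0.0015 and DE 1.75 to 1.90. Holding ICC at 0.007 instead implies k = 0.54 to 0.59.

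**Step 4: power for a 30% reduction (detectable effect at 80% power in brackets).** The last column uses 192 × 0.85 = 163 per 1000, a 12-month risk of 0.033 to 0.039.

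| Reading | 100/1000 | 163/1000 |
|---|---|---|
| Resident children, k held at 0.25 | 49–53% (40–42%) | 59–62% (36–38%) |
| Annual livebirths as the unit, ICC 0.007 | 50–54% (40–41%) | 74–78% (31–32%) |
| Resident children, ICC 0.007 | 20–24% (61–66%) | 31–36% (50–54%) |

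Worked example, first row at s = 5: effective n = 6080/1.75 ≈ 3465; 0.020 against 0.014; null and alternative standard errors both about 0.0031; (0.006 − 1.96 × 0.0031057)/0.003105 = −0.03; power 49%.

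The 74–78% entry keeps ICC at 0.007 at the higher risk, which lowers k to √(0.007 × 0.8368/0.1632) = 0.19. With k at 0.25 the ICC is 0.063 × 0.1632/0.8368 = 0.0123 and power is 61–64%.

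**The case against.** **Covered elsewhere.** The article promises to review the sample size assumptions after baseline, and its Discussion warns of low power if mortality has fallen faster than presumed or deaths are not reliably recorded. Both concern the mortality level. Entering an updated per-livebirth figure against 380 residents would repeat the mismatch, and the shortfall exists even if 100 per 1000 is exactly right and every death is found.

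**The baseline is conservative.** Going from 163 to 100 is a 1.6-fold allowance, smaller than the 4.2- to 5-fold overstatement. It does matter to the size of the problem: at 163 per 1000 on the livebirth reading, power is about what the article's own inputs deliver.

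**The open cohort adds children.** Births largely replace children who age out, so child-years stay near 380 per cluster and expected deaths do not rise materially.

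**The multiplier is external.** This stands. Residents per annual birth is an assumption, and the fold figure must be quoted with it.

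**The worst case is implausible.** This also stands. Power of 20–24% requires k to more than double, from 0.25 to 0.54–0.59. Nothing in the article supports that, and the scale on which the cited ICC was estimated is not shown. These figures are a lower bound, not the headline.

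**Part of the gap is separate.** The stated inputs give about 75% before any change of units, so the loss due to units is from about 75% to about 50%, not from 80%.

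**Conclusion.** The units do not match, and 80% power for a 30% reduction is wrong as stated. At 100 per 1000 livebirths and 4.2 to 5 resident under-fives per annual birth, power is about 49–54%, with a detectable effect of about 40–42%. This holds whether resident children are the unit with k at 0.25 or annual livebirths are the unit. The exact figure depends on the residents-per-birth ratio, on how clustering behaves at the lower risk, and on 16 clusters per arm. No clustered scenario examined reaches 80%.

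Two stronger readings are not supported. A reader might infer that a true 30% reduction would usually be missed; on the more plausible readings at 100 per 1000 it is about a coin flip, and at 163 per 1000 it would be detected more often than not. A reader might also infer that 80% is out of reach even without clustering; at 163 per 1000 the unclustered resident-child calculation gives 91–95%, so the conclusion rests on allowing for clustering. Nor does the article say that a null result would be read as evidence against the package; the risk is that its stated power invites that reading.

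**What to change.** At the planned post-baseline review, redo the calculation on the 12-month death risk, or rate per child-year, of resident children aged 7 days to 59 months, using the baseline birth histories and resident counts. Express the ICC or k on that same outcome, and show the residents-per-birth conversion if a per-livebirth rate is still used. State the number of clusters per arm and check that the inputs reproduce the quoted power.

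In the abstract and the Sample size section, replace the 30% detectable effect at 80% power with the result (about 40% on present assumptions). Add that a non-significant result would not exclude a 30% reduction.

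The cost is a recalculation and a wording change. No extra participants are needed; the stated figure becomes less favourable.

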### Data collection

Data collection will be done by 20 female clinical data collectors recruited from Jigawa, with two field supervisors. They will work in teams of 3–4, accompanied by a lay data collector to support community mapping. A sub-set of data collectors will be retained between surveys to conduct prospective vital event reporting. Data will be collected using a custom-built CommCare application on Android tablets. The forms will have in-built skip patterns and cleaning rules to minimise data entry errors. Data will be uploaded daily to a central secure server, and participant ID and data cleaning checks will be conducted continually during the data collection period. Data collectors will be trained using a hybrid approach, with a mix of practical sessions, at-home assignments and online webinars over a 2-week period. This will be followed by a field pilot in a neighbouring LGA and mock interviews with a group of women in the community who took part in questionnaire co-design discussions.

#### Baseline and endline surveys

The baseline and endline surveys are planned to take 3 months, with approximately 70 compounds completed each day. Three respondent types will be interviewed in each compound: (1) head of compound, (2) head of households and (3) eligible women. The head, or most senior member of the compound present at the time of the survey, interview will include compound membership, structure and construction; shared compound and individual household assets and income; and community cohesion. Household heads will be asked about household membership and asset ownership. Women will be asked about themselves, and then about each of the children under-five who are in their direct care. Questions include recent birth history, demographics and social status, knowledge of pneumonia, recent illness episodes and care-seeking, vaccination status, feeding practices, smoke exposure, community cohesion and wellbeing (using the Short Warwick-Edinburgh Mental Wellbeing Scale [23]). Questions on pneumonia knowledge and recent illness will use multi-media (i.e. videos and sounds) to provide examples of key signs and symptoms. In the endline survey, additional questions will be asked about intervention exposure and engagement.

A clinical screening for malnutrition and pneumonia will be conducted on all children aged 0–59 months who are present in the compound at the time of the survey. The assessment will follow the WHO’s 2014 IMCI guidelines [19﻿], enhanced with pulse oximetry using the Lifebox pulse oximeter (Acare Technology, New Taipei City, Taiwan). If a child is found with pneumonia, the data collector will inform the caregiver and advise them to seek care and facilitate referral in cases of severe illness.

#### Prospective vital event reporting

Following recruitment, the same compounds will be visited on a four-monthly rolling basis. All previously registered women will be asked about their current pregnancy status, the outcome of previously reported and completed pregnancies and the vital status of all registered children. Any new children under-five will be registered and included in the cohort. Verbal autopsies (VAs) will be conducted for all deaths in children under-five, including those reported in the prior 12 months from birth histories. This time period was chosen to minimise recall bias, but ensure a culturally appropriate period of time has passed since the death. We will use the COVID-19 adapted WHO 2016 VA tool and include locally adapted social autopsy questions which explore care-seeking pathways [29, 30].

### Analysis

The primary analysis will be intention-to-treat, comparing under-five mortality between intervention and control clusters over a 12-month period (July 2021–June 2022), using mixed-effects logistic regression, with fixed effects for the trial arm (intervention or control), and random effects to adjust for compound-level clustering and trial cluster. Data from the first 6 months of intervention implementation (January–June 2021) will be considered as a baseline period, before any intervention effect would be expected. Any imbalances in baseline characteristics between arms will be presented to the Trial Steering Committee (TSC), who will advise on whether the primary analysis should be adjusted for these. We will conduct a complete case analysis, where only children with confirmed survival outcomes will be included; a sensitivity analysis using multiple imputation will be done, if outcome data is found to be missing at random.

Secondary analyses, using the same mixed-effects model approach, will explore differences in pneumonia prevalence, coverage of prevent and protect indicators, knowledge and care-seeking between intervention and control clusters (Table 3). Changes in pneumonia prevalence, knowledge and care-seeking between baseline and endline surveys will be described and compared using chi-squared tests.

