### Design

This is a pragmatic community-based cRCT, following a formative phase of intervention development, concept testing and community engagement. Impact against the primary outcome will be evaluated using an open prospective cohort, recording vital events (pregnancies, births and under-five child deaths) amongst a random sample of women on a rolling 4-monthly basis. Secondary outcomes will be recorded during cross-sectional surveys conducted at baseline (January–March 2021) and end line (July–September 2022) (Fig. 1). The same random sample of compounds, and all eligible women and children residing in these compounds, will be included in both surveys and prospective cohort.

Clusters are defined as the geographical catchment area of the 33 government primary care facilities. Clusters range in population size from approximately 1680 to 24,200 (median 5840). All villages in Kiyawa LGA will be included in the study (*n* = 425 enumerated villages); however, the Kiyawa PHC cluster will be excluded from the impact evaluation as this facility is in a peri-urban area and provides a level of inpatient care—unlike the other primary facilities. Villages are made up of compounds, which are defined as the group of structures (including ‘households’) where extended families live and have shared resources.

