### Randomisation

The 33 clusters will be randomised using a 1:1 ratio between intervention and control. Randomisation will be done publicly, with representatives from the LGA and all the wards, following community consent for the study and the randomisation process. The names of the health facility clusters will be written on pieces of paper, folded and placed in a container by study staff. A community representative will then pull the folded pieces of paper out of the container one by one, in front of community witnesses. The first 17 will be assigned to the intervention, and the final 16 will be assigned to control. Due to the nature of the intervention, communities will not be blinded to their status; however, we will not inform data collectors of the intervention status of villages or that they work across intervention and control clusters, and investigators will be blinded during primary analysis.

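### The primary mixed-effects logistic model is tested on 32 clusters with no small-sample inference stated; the usual maximum-likelihood tests of it run at about 6-7%, not 5%

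*Protocol article*

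**What the plan says.** The Analysis section of the protocol article fixes the primary comparison as a mixed-effects logistic regression over July 2021 to June 2022, with a fixed effect for arm and "random effects to adjust for compound-level clustering and trial cluster". It gives no test statistic, reference distribution or degrees of freedom, and it does not rule out a correction.

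The inputs that matter are elsewhere in the article:

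- Abstract, Methods: "32 clusters included in the impact evaluation".
- Randomisation: "The first 17 will be assigned to the intervention, and the final 16 will be assigned to control". One cluster, Kiyawa PHC, is then left out of the impact evaluation (Design). The analysed split is therefore 16 v 16 if that cluster was drawn to intervention, and 17 v 15 if it was drawn to control.
- Sample size: "a) 380 children per cluster, (b) 80% power, (c) 5% significance", with an intra-cluster correlation (ICC) of 0.007 and a "coefficient of variance of cluster size of 0.74". The control risk is 100 per 1000.
- Design and Sampling: cluster populations run from about 1680 to 24,200. Compounds are sampled in proportion to cluster size, with at least 50 per cluster.

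**The concern.** Arm is assigned by cluster, so the arm effect is judged against variation among only 32 units. A maximum-likelihood fit tends to underestimate the between-cluster variance when clusters are few, and a normal or chi-square reference ignores the uncertainty in that estimate. Both errors make the p-value too small and the interval too narrow.

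Mortality is the single primary outcome, and the Discussion accepts that the trial may be under-powered. A result close to the threshold is therefore plausible, and there the gap between a true 7% level and a nominal 5% could decide the claim. The Analysis section uses the same model approach for the secondary outcomes; their error rates were not examined here.

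**Working it through.** **The plan's own figures.** The article states no attained type I error, so there is none to reproduce. Its sample size fixes the inputs:

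- 4480 / 32 = 140 compounds per cluster. Allowing 10% loss leaves 126, against the 127 stated. So 32 clusters is the number the plan used.
- Design effect = 1 + [(CV² + 1)m - 1] × ICC = 1 + [(0.74² + 1) × 380 - 1] × 0.007 = 5.11.
- Effective number per arm = 16 × 380 / 5.11 = 1190, against 1356 needed for 10% v 7% at 80% power. This gives power of 74.7%, and a detectable effect of 31.9% at 80% power.

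The stated 30% at 80% power is therefore not reproduced by this formula. A relative-efficiency design effect of 4.10 gives 83.4%. That is a separate matter and is not relied on here.

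**Rough size of the effect with equal clusters.** Referring a t statistic on 30 degrees of freedom to the normal cut-off gives P(|t₃₀| > 1.96) = 5.9%. If the variance is also too small by 30/32, the effective cut-off is 1.96 × √(30/32) = 1.898, and P(|t₃₀| > 1.898) = 6.7%. An error of about 6-7% is thus expected before unequal size enters.

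**Simulation under no effect.** The set-up was 32 clusters (16 v 16), mean 380 children, and skewed sizes matched to CV 0.74. The cluster variance on the logit scale was ICC / [p(1 - p)] = 0.007 / 0.09 = 0.078. A random-intercept logistic model was fitted by maximum likelihood with adaptive quadrature. There were 20,000 trials per row, so the Monte Carlo standard error is √(0.07 × 0.93 / 20,000) = 0.18 points. Tests are two-sided at nominal 5%; the article does not state sidedness.

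| Risk, ICC, CV | Wald z | Likelihood ratio | Wald t(30) | Cluster-level t |
|---|---|---|---|---|
| 10%, 0.007, 0.74 (plan) | 7.16% | 6.28% | 6.10% | 5.10% |
| Same, at least 150 children per cluster | 7.03% | 6.26% | 6.02% | 4.99% |
| 10%, 0.007, equal sizes | 6.31% | 5.66% | 5.45% | 4.78% |
| 8.5%, 0.007, 0.74 | 6.87% | 6.02% | 5.80% | 4.83% |
| 10%, 0.02, 0.74 | 6.83% | 6.12% | 5.89% | 4.90% |
| 10%, 0.002, 0.74 | 7.04% | 6.14% | 6.00% | 4.88% |
| 3%, 0.007, 0.74 | 6.98% | 6.09% | 5.79% | 4.79% |

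The 150-child floor is the plan's 50 compounds × 3 children.

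**Where the excess comes from.** At the plan's inputs the Wald z excess is 7.16 - 5 = 2.16 points. With equal clusters it is 6.31 - 5 = 1.31 points. Unequal size adds 7.16 - 6.31 = 0.85 points, so the small number of clusters explains most of it.

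**Second check.** A separate run of 4,000 trials at the plan's inputs gave 7.1% (Wald z), 6.3% (likelihood ratio), 5.9% (Wald t on 30 degrees of freedom) and 5.0% (cluster-level t). With compound-level heterogeneity added to the data, Wald z gave 7.2%.

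**Power cost.** In a further simulation of a 30% reduction (gamma sizes, the same floor), Wald z against a randomisation test had power 89.7% v 86.2% (10% risk, ICC 0.007), a loss of 3.5 points. At 2% risk and ICC 0.002 it was 54.0% v 46.9%, a loss of 7.1 points. Only these differences are used; the levels are not comparable with the formula above.

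**The case against.** The strongest reply is that the article is silent rather than wrong. It names a model and not a test. A condensed article may leave the reference distribution to the full protocol or an analysis plan, neither of which is shown. The 5% is a sample-size input and does not describe how the p-value will be computed. All of that stands. A reader might infer that the plan has chosen an uncorrected Wald z test; the article does not say so, and the point is conditional for that reason.

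Silence is not a full answer, however. All three maximum-likelihood tests examined exceed 5% at the plan's inputs, including the obvious repair of a t reference on 30 degrees of freedom. Choosing among them later would not deliver the stated level.

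Two stronger readings fail:

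- A reader might put the true level at 7-8%. A smaller simulation (standard error about 0.45 points) did give 7.2-7.8% for Wald z. But its randomisation test came out at 5.5-5.8% and its cluster-level t test at about 5.5%, where 5% is expected, which suggests that the run was somewhat high throughout. No row of the larger simulation reached 7.5%.
- A reader might blame the very unequal clusters. They add under 1 point.

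It is also fair that the main simulation fitted no compound-level random effect, which the plan's model includes.

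**Conclusion.** The point holds in conditional form. If the stated model is fitted by maximum likelihood and tested in a standard way, the two-sided type I error is about 7% by Wald z and about 6% by likelihood ratio or Wald t on 30 degrees of freedom. Under no effect, a nominal 95% Wald z interval would then cover about 93% of the time. At CV 0.74 the Wald z figure stays within 6.8-7.2% for ICCs of 0.002-0.02 and risks of 3-10%, so it does not hang on the assumed 10% baseline.

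The result assumes a two-sided test, a 16 v 16 split, a skewed size distribution matched to CV 0.74, and a fit with the cluster effect only. Adding compound-level heterogeneity to the data left Wald z much the same. The inflation is modest: it matters for a borderline result and would not overturn a clear one.

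**What to change.** Keep the mixed-effects model for the point estimate. Add a sentence, fixed before outcomes are seen, stating that the primary p-value and confidence interval come from a method that holds 5% with 32 clusters. Any of these would serve:

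- A randomisation test that re-labels the 32 analysed clusters as the unrestricted public draw did, holding the realised split (16 v 16 or 17 v 15), with the interval obtained by inverting the same test.
- A cluster-level t analysis, which held 5.0-5.1% at the plan's inputs. Its interval should be reported with its own effect measure, because it is not on the odds-ratio scale of the mixed model.
- Restricted pseudo-likelihood with a Kenward-Roger correction. This keeps estimate and interval on one scale, but it was not simulated here and should be checked with about three children per compound.

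The sentence should also say how the method handles any covariates that the Trial Steering Committee advises adding. If the analysis plan already specifies a suitable method, a citation is enough.

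The cost is a sentence, some computing, and roughly 3-7 points of power for the randomisation test against uncorrected Wald z, part of which is only the removal of the inflation. Power for the other two options was not simulated.

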### Population

The target population for the impact evaluation is women of childbearing age, defined as 16–49 years inclusive, and children aged 0–59 months inclusive, who reside permanently in Kiyawa LGA. Women and children will be considered lost to follow-up if they migrate, are temporarily unavailable, or consent is withdrawn. Children of women who are lost to follow-up, or die during the study period, will still be included if they continue to reside in the same compound and an eligible caregiver can provide consent. The intervention is open to all community members, with no age or gender restrictions.

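### The primary model is a complete-case logistic regression on an open cohort: it ignores time at risk and drops living leavers, which distorts the mortality level and can bias the arm comparison if entry or loss differs by arm

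*Protocol article*

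**What the plan says.** All references are to the protocol article.

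- **Design:** "Impact against the primary outcome will be evaluated using an open prospective cohort". Under Prospective vital event reporting, compounds are revisited every four months and "Any new children under-five will be registered and included in the cohort".
- **Population:** "Women and children will be considered lost to follow-up if they migrate, are temporarily unavailable, or consent is withdrawn". Children whose mother is lost or dies stay in if they remain in the compound and another eligible caregiver consents.
- **Analysis:** the primary analysis is by intention to treat, "comparing under-five mortality between intervention and control clusters over a 12-month period" (July 2021 to June 2022), "using mixed-effects logistic regression, with fixed effects for the trial arm (intervention or control") and random effects for compound and trial cluster. On missing outcomes: "We will conduct a complete case analysis, where only children with confirmed survival outcomes will be included". The same sentence continues: "a sensitivity analysis using multiple imputation will be done, if outcome data is found to be missing at random".
- **Outcome:** the text divides deaths by resident children, and Table 3 divides them by live births. Neither is child-time. Table 3 counts only deaths verified at a verbal autopsy visit.

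No offset, censoring rule or time-to-event term is stated. The model and the analysis set are fixed here, so this is not a detail left open for an analysis plan.

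**The concern.** Each choice is explicit, but together they do not fit an open cohort.

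First, a yes/no outcome over a fixed window presumes the same opportunity to die for every child. Children born or arriving late in the window, or reaching their fifth birthday early in it, do not have that.

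Second, the complete-case rule depends partly on the outcome. A child whose death was verified before the family moved has a confirmed outcome and is kept. A child seen alive for eight months whose family then moves may have none and is dropped, with those eight months. This selection arises even when moving has nothing to do with the risk of death, because a child who has died cannot later be lost alive.

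At stake are the mortality level reported in each arm and, if the arms differ in entry or loss, the primary effect estimate. Communities know their allocation (Randomisation) and one arm receives intensive mobilisation, so a difference is possible. The documents give no evidence that one will occur.

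**Working it through.** **Inputs from the protocol article.** A 12-month window, four-monthly rounds and ages up to 59 months. Design mortality is 100 per 1000 live births, with a 30% reduction targeted. Loss to follow-up is about 10% (Sample size). That allowance reproduces: 127 × 32 = 4,064 compounds, and 4,480 / 4,064 = 1.10. It is an overall figure for compounds; none is given by arm. The plan gives no figure for the bias itself.

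**Assumptions.** Constant hazard; entry and leaving uniform over the window; leaving unrelated to death. The documents give no 12-month risk per child, so I use p = 0.10 (the design figure read as a risk) and p = 0.02. Loss L is 5% to 20% and late entry 15% to 25%.

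**Step 1: how unequal is exposure?** With a stable age structure and no migration or deaths, 12/60 = one-fifth of a standing cohort of N is born in during the year and one-fifth ages out. Of 1.2N children ever present, 0.4N (one-third) have partial exposure, averaging six months. Late entrants are 0.2/1.2 = 17% of the total. At p = 0.10, one month carries a risk of 1 − 0.90^(1/12) = 0.0087, yet that child weighs as much as one followed all year.

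**Step 2: loss alone.** Leavers are exposed for half the window on average.

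- Deaths kept: p(1 − L/2)
- Complete cases: 1 − L + Lp/2
- Complete-case risk: p(1 − L/2) / (1 − L + Lp/2)

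| L | Risk at p = 0.10 | Inflation at p = 0.10 | Inflation at p = 0.02 |
|---|---|---|---|
| 5% | 0.102 | 1.024 | 1.026 |
| 10% | 0.105 | 1.050 | 1.054 |
| 15% | 0.108 | 1.079 | 1.086 |
| 20% | 0.111 | 1.111 | 1.122 |

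Survivors kept are (1 − L)(1 − p), so the complete-case odds are p/(1 − p) × (1 − L/2)/(1 − L). The multiplier does not depend on p, so equal loss in both arms cancels from the odds ratio. For unequal loss and no true effect:

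- Multiplier at 5%: 0.975/0.95 = 1.026
- Multiplier at 15%: 0.925/0.85 = 1.088
- Intervention arm loses 5%, control 15%: 1.026/1.088 = 0.94
- Intervention arm loses 15%, control 5%: 1.088/1.026 = 1.06

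**Step 3: late entry alone.** With a share e entering late, the risk is p(1 − e/2). At e = 20% and p = 0.10 it is 0.090, a fall of 10%. With e = 15% in control, 25% in intervention and no true effect, the risk ratio is 0.875/0.925 = 0.95.

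**Step 4: both together.** Simulation of 4 million children per arm with control risk 0.10, a true odds ratio of 0.677 and a true rate ratio of 0.689:

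| Loss, control / intervention | Late entry, control / intervention | Complete-case control risk | Odds ratio | Child-time rate ratio |
|---|---|---|---|---|
| 10% / 10% | 20% / 20% | 0.0945 | 0.681 | 0.691 |
| 20% / 20% | 20% / 20% | 0.1002 | 0.680 | 0.690 |
| 5% / 15% | 20% / 20% | 0.0921 | 0.722 | 0.690 |
| 15% / 5% | 20% / 20% | 0.0972 | 0.642 | 0.690 |
| 10% / 10% | 15% / 25% | 0.0970 | 0.642 | 0.690 |
| 10% / 10% | 25% / 15% | 0.0919 | 0.723 | 0.691 |

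The pattern at p = 0.02 is the same.

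**The case against.** The strongest reply is that the primary analysis is a comparison of arms, and with balanced entry and loss that comparison is almost untouched (0.68 against 0.677). This stands. The unequal splits are assumptions, and the protocol article reports only an overall loss allowance.

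The plan also has safeguards:

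- Multiple imputation is planned and is relevant to the missing outcomes. It does not deal with late entry or ageing out. It is also conditional on a finding that observed data cannot deliver, since they cannot show outcomes to be missing at random.
- A confirmed outcome is not defined as being seen at the last round. The endline survey revisits the same compounds in July to September 2022 and can recover children who were only temporarily away. That narrows the problem to those who have really left.

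A reader might infer four stronger things that the documents do not support:

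- **That mortality is inflated in both arms.** Loss alone would do that, but late entry pulls down. With 20% late entry and 10% loss the level falls from 0.100 to 0.0945.
- **That the trial is tilted towards showing a benefit.** The same imbalance placed in the other arm hides a benefit.
- **That every death before leaving is kept.** A death counts only once verified, so a family leaving between rounds may take it out of the data.
- **That the intention-to-treat claim is false.** Clusters are compared as allocated; missing outcomes are a separate matter.

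**Conclusion.** The point holds in a limited form. A complete-case logistic model does not suit an open cohort with rolling entry: it ignores time at risk and discards the observed survival of living leavers while verified deaths count. The mortality level is distorted by roughly 5% to 10% in either direction at the loss and late-entry shares considered, and the net sign cannot be fixed in advance.

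The arm comparison is biased only if entry or loss differs by arm. A ten-point difference in either moves the odds ratio by about 6%, in a direction set by which arm has more. That compares with a 30% target effect. With balanced arms the bias is negligible.

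These sizes rest on uniform timing, constant hazard, loss unrelated to death, and assumed shares that the documents do not give. The change is worth making because it is cheap and removes the dependence on balance, not because the planned comparison is known to be wrong.

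**What to change.** Make the primary analysis a mixed-effects Poisson (or piecewise exponential) model of deaths with a log child-time offset, arm as fixed effect, and random effects for cluster and compound.

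- **Entry:** for registered children and all children born to registered women, the later of 1 July 2021 and day 7 of life. This must include children born and dead between rounds, whose deaths are captured through pregnancy outcomes; starting everyone's time at registration would lose them. For other new children, use the date of joining the compound or of registration, if later.
- **Exit:** the earliest of death, fifth birthday, date last known alive in the compound, and 30 June 2022.
- **Sensitivity analyses:** keep the complete-case logistic model and the multiple imputation, and report entry and loss by arm.

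The cost is analysis wording and programming, with no extra visits. The effect becomes a rate ratio rather than an odds ratio. Some entry and exit dates will be known only to within a four-monthly round, so a dating convention must be written down. The method still assumes that loss is unrelated to death.
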